### Randomization and recruitment

2.7

The randomization procedure will be managed and documented entirely by an independent statistician who is not engaged in the implementation of the study. Sixty-four random numbers were generated using IBM SPSS Statistics (v.25.0; IBM Corp., Armonk, NY). These random numbers will then be allocated equally to two groups using the visual split-box function in SPSS. Another designated blinded investigator is responsible for assigning participants to different interventions. To ensure allocation concealment, other investigators, including participant recruiters and evaluators, will remain unaware of the randomization results until the study is fully completed. Using this approach, the study will effectively accomplish randomization and allocation concealment, thereby minimizing selection bias and ensuring the validity and reliability of the results.

The intended recruitment period is approximately 2 years and 2 months, from 28 December 2024, to 28 February 2027. The participants will be free to withdraw from the study at any time. The reasons for withdrawal will be documented. If the reason is associated with adverse events, it will be followed up until the issue is completely resolved. Participants who have received other treatments or participated in another program related to BSP therapy during the trial will be considered dropouts.

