### Objectives and endpoints

2.3

Primary objectives: The study primarily aims to evaluate the clinical effects of topical FEO combined with BoNT injections in patients with BSP. Specifically, we will compare the topical FEO group with the CO group in terms of the duration of symptom improvement, quality of life, and self-rating of response to efficacy during a 24-week follow-up. Symptom improvement is defined as a decrease of one point or more in the JRS severity in the JRS severity score relative to baseline in patients with BSP (24). We hypothesized that, unlike the placebo group, topical FEO combined with BoNT will significantly prolong the duration of symptom improvement, improve patient rating of quality of life, and self-rating of response to efficacy, with acceptable safety at the 24-week follow-up.

The primary endpoint is the duration of symptom improvement over 24 weeks, as defined above.

The secondary endpoint of the study is the percentage change from baseline to different time points in the physician rating of the BSP. This involves motor symptom severity, measured by the JRS (25), the Blepharospasm Severity Rating Scale (BSRS) (26), and the Burke Fahn Marsden’s Dystonia Rating Scales (BFMDRS) (27), and quality of life, assessed by the Blepharospasm Disability Index (BSDI) (25), the Short Form-36 Health Survey (SF-36) (28), and the Cranio-cervical Dystonia Questionnaire (CDQ-24) (29). In addition, patient subjective ratings via the Patient Evaluation of Global Response (PEGR) and the incidence of adverse events will be included (30).

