### Safety evaluation

2.5

Based on previous studies, the oral use of frankincense occasionally or rarely causes adverse reactions such as eczema, nausea, aggravation of arthralgia, and gastrointestinal symptoms (20, 36, 37). Topical application of FEO has fewer side effects, predominantly in the form of localized skin allergic reactions (38). All adverse events, including their description, duration, severity, and required treatment, will be documented and treated with care. Any serious adverse events will be immediately reported to the chief investigator and ethics committee of the First Affiliated Hospital of Sun Yat–sen University, and the ethics committee will ultimately determine the termination of the study.

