### Trial assessment and follow-up

2.9

Full eligibility criteria will be assessed and confirmed before randomization. Further assessments should be conducted at multiple time points. An overview of the data collection process is provided in Table 2. Data will be collected from all participants until they complete the 24-week follow-up period or discontinue the study.

**Table 2 tab2:** Time and events.

Description	Screening	Day 0	2nd week	4th week	8th week	12th week	16th week	20th week	24th week
Consent	**√**								
Neurological exam	**√**								
Medical history	**√**								
Inclusion/exclusion	**√**								
Randomization	**√**								
MRI	**√**								
Baseline assessment	**√**								
Motor symptom assessment	**√**		**√**	**√**	**√**	**√**	**√**	**√**	**√**
Quality-of-life assessment	**√**		**√**	**√**	**√**	**√**	**√**	**√**	**√**
Video recording	**√**		**√**	**√**	**√**	**√**	**√**	**√**	**√**
PEGR			**√**	**√**	**√**	**√**	**√**	**√**	**√**
Non-motor symptom assessment	**√**					**√**			**√**
Blinded rater evaluation	**√**	**√**	**√**	**√**	**√**	**√**	**√**	**√**	**√**
BoNT injection		**√**							
FEO/CO application			**√**	**√**	**√**	**√**	**√**	**√**	**√**
Clinical assessments	**√**	**√**	**√**	**√**	**√**	**√**	**√**	**√**	**√**
Safety assessment	**√**	**√**	**√**	**√**	**√**	**√**	**√**	**√**	**√**

BoNT, botulinum toxin; CO, coconut oil; FEO, frankincense essential oil; MRI, magnetic resonance imaging; PEGR, Patient Evaluation of Global Response.

Patients will be withdrawn for the follow-up during a 24-week observation period if they meet any of the following three conditions: (1) the subject receives a BoNT-A reinjection during the follow-up period, (2) the JRS score returns to the baseline score, or (3) completion of a 24-week follow-up visit.

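### Follow-up ends at efficacy-related exits, so the 24-week safety statement would rest on about 11–15 weeks of observation, longer on FEO than on CO if FEO works

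*Protocol article*

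**What the plan says.** Five places in the protocol article bear on this point.

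- **Section 2.9 (Trial assessment and follow-up), exit rules:** "Patients will be withdrawn for the follow-up during a 24-week observation period if they meet any of the following three conditions". Two of the three can occur before week 24: "the subject receives a BoNT-A reinjection during the follow-up period" and "the JRS score returns to the baseline score". The third is completing the week-24 visit.
- **Section 2.9, end of data collection:** "Data will be collected from all participants until they complete the 24-week follow-up period or discontinue the study". Table 2 in the same section ticks safety assessment at every visit to week 24.
- **Section 2.3 (Objectives and endpoints):** the hypothesis includes a result "with acceptable safety at the 24-week follow-up", and the incidence of adverse events is listed with the secondary endpoints.
- **Section 2.5 (Safety evaluation):** "All adverse events, including their description, duration, severity, and required treatment, will be documented and treated with care". This carries no condition on why a patient leaves.
- **Section 2.7 (Randomization and recruitment):** after saying that participants may withdraw and that reasons will be recorded, it adds "If the reason is associated with adverse events, it will be followed up until the issue is completely resolved".

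Section 2.6 gives the planning values for duration of benefit: 75 days (SD 15) on CO and 90 days (SD 18.5) on FEO. The latter averages responders at 105 days and non-responders at 75 days.

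**The concern.** The efficacy-related exits in section 2.9 also appear to end safety observation, because data are collected until completion or discontinuation and nothing separates safety data from the rest. Two consequences follow.

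1. The trial recruits patients whose benefit from BoNT lasts less than 12 weeks and plans for mean benefit of 75 and 90 days. Most would leave well before week 24, so the later safety visits in Table 2 would be largely empty and could not support a statement about safety at 24 weeks.
2. The length of the safety window depends on the treatment effect. If FEO prolongs benefit, the FEO arm is watched longer and collects more events at the same underlying rate. A crude comparison of percentages would then count against FEO because it works.

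There is also a gap in the wording. Section 2.5 asks for the duration of every adverse event. Section 2.7 states follow-up to resolution for withdrawals related to adverse events. For an event still ongoing when a patient leaves under section 2.9, the article does not say how the duration would be obtained. The main risk named in section 2.5 for topical FEO is local skin allergy, and the oil is applied to the eyelids twice daily (section 2.8.1), so the length of observation matters to the safety conclusion.

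**Working it through.** **Inputs.** From section 2.6: duration of benefit 75 ± 15 days (CO) and 90 ± 18.5 days (FEO); 32 recruited per arm. From section 2.4: visits at weeks 2, 4, 8, 12, 16, 20 and 24. Full follow-up is 24 weeks, or 168 days.

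**The plan's own figure.** A difference of 15 days with SD 18.5 in both arms, two-sided 5% level and 80% power gives 2 × (1.960 + 0.842)² × 18.5² / 15² = 23.9, so 24 per arm by the normal approximation. The exact t-test calculation gives 25 (power 0.802), as stated. With 20% loss (a rate the article does not give), 25 / 0.80 = 31.25, rounded up to 32. The sample size is not in dispute; this only confirms the reading of the inputs.

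**Assumptions for what follows.** Loss of benefit is the time of exit, durations are normal, and there is no other dropout.

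**Mean observation if exit occurs on the day benefit ends.**

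- CO: 75 / 7 = 10.7 weeks (75 / 168 = 45% of full follow-up)
- FEO: 90 / 7 = 12.9 weeks (90 / 168 = 54%)
- Ratio: 90 / 75 = 1.20

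**Share still benefiting.** S(t) = 1 − Φ((t − mean) / SD), times 32 for the expected number of patients:

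| Week (day) | CO: S, of 32 | FEO: S, of 32 |
|---|---|---|
| 8 (56) | 0.897, 28.7 | 0.967, 30.9 |
| 12 (84) | 0.274, 8.8 | 0.627, 20.1 |
| 16 (112) | 0.007, 0.2 | 0.117, 3.7 |
| 20 (140) | 0.000, 0.0 | 0.003, 0.1 |
| 24 (168) | 0.000, 0.0 | 0.000, 0.0 |

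Modelling FEO as a 50:50 mixture of 75 ± 15 and 105 ± 15 days gives 19.1, 5.2, 0.2 and 0.0 patients at weeks 12, 16, 20 and 24. The picture is the same.

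**Mean observation if exit is detected at the next scheduled visit.** This is the sum, over the gaps between visits, of the gap length times the share still benefiting at its start:

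- CO: 2 + 2(1.000) + 4(0.999) + 4(0.897) + 4(0.274) + 4(0.007) + 4(0.000) = 12.7 weeks (53% of 24)
- FEO: 2 + 2(1.000) + 4(1.000) + 4(0.967) + 4(0.627) + 4(0.117) + 4(0.003) = 14.9 weeks (62% of 24)
- Ratio: 14.86 / 12.71 = 1.17

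On this basis the table moves by one visit: those attending week 12 are the 28.7 and 30.9 still benefiting at week 8, and those attending week 24 are the 0.0 and 0.1 still benefiting at week 20. Fewer than one patient in either arm is expected at week 24 on either basis.

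**Patient-years for 32 per arm.** 6.6 (CO) and 7.9 (FEO) with exit on the exact day, or 7.8 and 9.1 with exit at the next visit, against 32 × 168 / 365.25 = 14.7 for complete follow-up.

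**Effect on crude incidence (illustration).** Take 20% incidence on CO and the same constant event rate in both arms; neither comes from the article. Applied to mean observation time, incidence on FEO is 1 − 0.80^ratio:

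- ratio 1.20: 1 − 0.80^1.20 = 23.5%
- ratio 1.17: 1 − 0.80^1.17 = 23.0%

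Of 32 patients that is 6.4 on CO against about 7.3 to 7.5 on FEO.

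**The case against.** **Nothing says that reactions are dropped.** A reader might infer that events are followed to resolution only when they cause withdrawal, and that a patient leaving for an efficacy reason is released with an unresolved reaction. The document does not support that. The sentence in section 2.7 says what happens in one case and excludes no other, and section 2.5 commits to documenting and treating all events, including their duration. What remains is that sections 2.5, 2.7 and 2.9 are not reconciled for an event ongoing at a section 2.9 exit.

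**A condensed article leaves such detail elsewhere.** Procedures for events ongoing at exit, and exposure-adjusted rates, may well be in the full protocol or the analysis plan. That is fair, and their absence alone would not be a finding. But the exit rules, the end of data collection, the 24-week hypothesis and the week-24 safety visits are all printed here and do not fit together.

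**The exposure figures are derived, not stated.** This stands. The section 2.6 durations describe clinical benefit; the exit rule refers to the JRS score returning to baseline, while the primary endpoint uses the JRS severity score. A flat figure of 11–13 weeks ignores visit spacing, hence the range of 11–15 weeks. Reinjection between visits could shorten the visit-based figures. Leaving follow-up also need not mean stopping the oil; the article does not say.

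**The bias is small.** It is about one patient per arm in the illustration, and section 2.10 specifies no test of adverse-event incidence between arms. Both are true. A larger figure based on responders at 105 days would describe half of the FEO arm and is not an arm comparison. The shortfall against 24 weeks is the larger effect.

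**Contacts after exit do not create exposure.** Calls to patients no longer using the oil say nothing about 24 weeks of use, and events after reinjection mix with a new BoNT cycle. This is why oil use must be recorded and why limiting the claim is a legitimate alternative.

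**Conclusion.** The point holds as a mismatch between the exit rules and the safety claim. With loss of benefit at the section 2.6 values taken as exit, mean safety observation is about 11–15 weeks, or 45–62% of the planned 24. It is 17–20% longer on FEO, and fewer than one patient per arm is expected to remain at week 24. A 24-week safety statement would therefore have almost no late observation behind it, and crude incidence would be compared over windows that depend on the treatment effect.

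The shortfall follows from the planning values under either way of timing exit. The unequal windows also require FEO to prolong benefit as hypothesised, and the shift from 20% to 23–23.5% requires in addition the assumed incidence and constant rate, so it shows direction and rough size only. The handling of events ongoing at exit is a gap to be reconciled, not evidence that patients go unfollowed.

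**What to change.** 1. **Section 2.9:** state that reinjection and return of the JRS score to baseline do not end safety data collection. Keep the safety contacts already in Table 2 to week 24, by telephone where suitable, and record at each whether the oil is still in use and whether BoNT-A has been repeated.
2. **Sections 2.3, 2.5, 2.7 and 2.9:** reconcile them on how an adverse event ongoing at a section 2.9 exit is followed, so that the duration required by section 2.5 can be recorded whatever the reason for exit.
3. **Reporting:** give adverse events per patient-week of observed oil use alongside the percentage of patients, with the observation time in each arm.
4. **If safety follow-up is not extended:** reword the 24-week safety hypothesis in section 2.3 and limit the conclusion to the exposure actually observed.

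The cost is protocol wording and some extra contacts at time points already scheduled, or else a safety claim for a shorter exposure. The sample size does not change.

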### Intervention administration

2.8

#### Topical FEO combined with BoNT group

2.8.1

Participants in the experimental group will receive injections of BoNT-A (Hengli, Lanzhou Biological Products Institute, Lanzhou, China; 100 U, diluted in 2 mL saline), using 1 mL syringes and manual targeting techniques. BoNT-A will be routinely administered to the orbicularis oculi muscles at a total of 10 points (5 points on each side). These points encompass the medial and lateral one-third of both the upper and lower eyelids, 2–3 mm from the eyelid margin, and the temporal orbicularis oculi muscle, located 5 mm from the lateral canthus. The corrugator supercilii muscles will receive two injections (one point on each side) located above the inner side of the eyebrows. Additionally, BoNT-A will be injected into the procerus muscle at a central point between the eyebrows. Each point will receive injection of 2.5 U BoNT-A, and the total BoNT-A dosage will be approximately 32.5 U per participant (Figure 2). The injection site and dosage will be adjusted slightly based on the patient’s condition. The next day, participants in the experimental group will begin applying the FEO mixture to the bilateral upper and lower eyelids twice daily, using 0.25 mL of the mixture per application, 0.125 mL for each side. The application will be performed after cleaning the face, and participants will be instructed to gently massage the oil mixture into the skin and rest with their eyes closed to allow absorption.

**Figure 2 fig2:**
[figure not shown]
Schematic diagram of BoNT-A injection sites. (1) Injection sites on the orbicularis oculis. (2) Injection sites on the procerus muscle. (3) Injection sites on the corrugator supercilii muscles. The doses of BoNT-A: 2.5 U/dot.

#### Topical CO combined with BoNT group

2.8.2

In the control group, the method of injecting BoNT-A and CO will be consistent with that of the experimental group, including site, dosage, and frequency. Participants will be provided with detailed instructions and training on the correct application of the oils, and their adherence to the intervention protocol will be monitored through regular follow-ups. FEO and CO used in the trial are supplied by Aromatics International.^1^

### Trial assessment and follow-up

2.9

Full eligibility criteria will be assessed and confirmed before randomization. Further assessments should be conducted at multiple time points. An overview of the data collection process is provided in Table 2. Data will be collected from all participants until they complete the 24-week follow-up period or discontinue the study.

**Table 2 tab2:** Time and events.

Description	Screening	Day 0	2nd week	4th week	8th week	12th week	16th week	20th week	24th week
Consent	**√**								
Neurological exam	**√**								
Medical history	**√**								
Inclusion/exclusion	**√**								
Randomization	**√**								
MRI	**√**								
Baseline assessment	**√**								
Motor symptom assessment	**√**		**√**	**√**	**√**	**√**	**√**	**√**	**√**
Quality-of-life assessment	**√**		**√**	**√**	**√**	**√**	**√**	**√**	**√**
Video recording	**√**		**√**	**√**	**√**	**√**	**√**	**√**	**√**
PEGR			**√**	**√**	**√**	**√**	**√**	**√**	**√**
Non-motor symptom assessment	**√**					**√**			**√**
Blinded rater evaluation	**√**	**√**	**√**	**√**	**√**	**√**	**√**	**√**	**√**
BoNT injection		**√**							
FEO/CO application			**√**	**√**	**√**	**√**	**√**	**√**	**√**
Clinical assessments	**√**	**√**	**√**	**√**	**√**	**√**	**√**	**√**	**√**
Safety assessment	**√**	**√**	**√**	**√**	**√**	**√**	**√**	**√**	**√**

BoNT, botulinum toxin; CO, coconut oil; FEO, frankincense essential oil; MRI, magnetic resonance imaging; PEGR, Patient Evaluation of Global Response.

Patients will be withdrawn for the follow-up during a 24-week observation period if they meet any of the following three conditions: (1) the subject receives a BoNT-A reinjection during the follow-up period, (2) the JRS score returns to the baseline score, or (3) completion of a 24-week follow-up visit.

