### Sample size

2.6

The sample size was calculated using the two-sample t-test method in PASS 15 software (NCSS, LLC, Kaysville, Utah, USA), with a two-sided significance level of 0.05 and a power of 0.8. Based on preliminary clinical observations obtained in our center, topical FEO alone was effective in approximately 50% of patients with BSP. This finding, combined with a conservative estimate of efficacy, prompted a reassessment of the required sample size to ensure adequate statistical power. The revision was implemented after trial initiation but prior to completion of participant recruitment, and constitutes an important protocol modification based on internally generated data. To determine the mean and standard deviation (SD) needed for the sample size calculation, we retrospectively analysed data from 61 patients with BSP at our movement disorders clinic who had received standard BoNT-A treatment and met the study’s inclusion criteria. After receiving their last three consecutive BoNT-A injections, these patients experienced clinical benefits for less than 3 months each time, demonstrating consistently unsatisfactory therapeutic effects. The mean duration of clinical benefits was 73.99 days (SD = 14.28). Given that the control group will receive a placebo, there may have been greater variability in the therapeutic effects due to individual response and disease progression; therefore, we decided to round the mean value to 75 days and the SD to 15 (i.e., 75.0 ± 15.0) to ensure robustness in the calculation. In this study, we hypothesized that combining BoNT-A injection with topical FEO would extend the effective duration of symptom relief by 30 days to 105.0 ± 15.0 days. Given an expected effective rate of only 50%, we estimated the mean duration of benefit in the experimental group as 90.0 ± 18.5 days, reflecting a weighted average between responders and non-responders. The resulting sample size calculation indicated N1 = N2 = 25, meaning that 25 participants are required for each group. Considering the participant loss to follow-up, we determined that each group would recruit 32 participants. A professional statistician verified the sample size calculation method. The amended protocol was reviewed and approved by the Ethics Committee of the First Affiliated Hospital of Sun Yat–sen University.

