### Statistical analysis

2.10

Trial analysis will be performed on an intention-to-treat (ITT) population. No interim analyses will be performed. A full statistical analysis plan will be developed before the final analysis.

Assumptions for parametric tests will be evaluated before analysis. Normality will be assessed using the Shapiro–Wilk test and Q-Q plots, and homogeneity of variances with Levene’s test. If these assumptions are not met, non-parametric alternatives will be used.

Missing data will be handled under the ITT principle, using all available observations without imputation beyond the last completed visit. Mixed-effects models will be used for repeated-measures secondary outcomes under the missing-at-random assumption. A per-protocol sensitivity analysis will also be conducted.

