## Discussion

3

This study will examine whether adding FEO to BoNT therapy can prolong symptom relief. It will also assess whether this combination improves quality of life compared to BoNT alone. In addition, the safety of topical FEO and CO will be evaluated. Sixty-four subjects will be randomized into two groups, with assessments conducted at multiple time points during a 24-week follow-up period. Outcomes will include the duration of symptom improvement, quality of life, and self-rating of response to efficacy, providing evidence of whether FEO therapy is an effective adjunct therapy for the control of BSP symptoms.

However, certain practical issues require clarification. Because FEO has a strong and characteristic odor that cannot be masked even when diluted or sealed, an open-label design was necessary (39). To minimize subjective bias, all assessments will be conducted by two independent blinded evaluators using the same evaluation protocol. Because pure FEO causes irritation when applied directly to the skin, it must be diluted 1:1 with a carrier oil such as CO (16). In this study, CO was chosen as the diluent, but its potential effects on BSP are unknown. Therefore, to control for any influence of CO itself, the control group will receive topical CO alone, applied using the same dosage and massage procedure as in the experimental group.

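### Follow-up ends at reinjection with no blinded JRS rating then, so the end of the primary duration can go unseen and may depend on treatment-seeking by patients who know their arm

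*Protocol article*

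**What the plan says.** All references are to the protocol article.

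- **Outcome.** Sections 2.3 and 2.10.2 define the primary outcome as the time during which JRS severity stays at least one point below baseline, over 24 weeks. Arms are compared by t-test or Mann–Whitney test.
- **End of follow-up.** Section 2.9 lists three conditions. The first is "1) the subject receives a BoNT-A reinjection during the follow-up period". Return of the JRS score to baseline is a separate second condition, so reinjection ends observation whatever the score is.
- **Other treatment.** Section 2.7: "Participants who have received other treatments or participated in another program related to BSP therapy during the trial will be considered dropouts".
- **Blinding.** The Discussion explains that "FEO has a strong and characteristic odor that cannot be masked even when diluted or sealed, an open-label design was necessary". Section 2.4 assigns the ratings to two blinded evaluators at each visit.
- **Schedule.** After baseline, Table 2 places motor ratings and video at weeks 2, 4, 8, 12, 16, 20 and 24. It has no column for exit or for the day of reinjection.
- **Missing data.** Section 2.10 specifies intention-to-treat, "using all available observations without imputation beyond the last completed visit".
- **Related outcome.** The interval between BoNT treatments is a separate secondary outcome (Table 1, Section 2.10.3).

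**The concern.** In an open-label trial, blinded rating is the main safeguard for a rated outcome. Here it protects each scheduled score but not the moment at which observation stops. A patient can be reinjected between two visits, and no blinded evaluator records whether benefit had gone by then. The patient knows which oil was used, and the article gives no criterion for reinjection. Willingness to wait for the next visit could therefore differ between arms for reasons unrelated to JRS severity.

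Two things are at stake. The loss of benefit may never be rated in a sizeable share of patients, and that share may differ by arm. A patient reinjected while still one point better would also leave no record of it. A later analysis plan can choose a scoring rule, but it cannot recover a rating that was never taken.

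**Working it through.** **1. The plan's own figure.** Section 2.6 sets the test "with a two-sided significance level of 0.05 and a power of 0.8". For controls, "we decided to round the mean value to 75 days and the SD to 15 (i.e., 75.0 ± 15.0" days. For the experimental arm, "we estimated the mean duration of benefit in the experimental group as 90.0 ± 18.5 days". The planned difference is 90 − 75 = 15 days. A two-sample t-test with SD 18.5 in both arms and n = 25 has noncentrality 15 / (18.5 × √(2/25)) = 15 / 5.23 = 2.87 on 48 degrees of freedom, which gives power 0.802. With n = 24 power is 0.785. So "The resulting sample size calculation indicated N1 = N2 = 25" is reproduced. The 32 recruited per arm fits a 20% loss: 25 / 0.80 = 31.25, rounded up. No loss rate is stated.

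**2. How many patients lose benefit between two ratings.** Weeks 8 and 12 are days 56 and 84. On the control assumption N(75, 15):

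P(56 ≤ D < 84) = Φ((84 − 75)/15) − Φ((56 − 75)/15) = Φ(0.60) − Φ(−1.27) = 0.726 − 0.103 = 0.623.

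About 62% would therefore lose benefit inside one 28-day gap. The Introduction says most patients are reinjected after 12 weeks or 4–5 times a year, that is about every 365/5 = 73 to 365/4 = 91 days. Reinjection before the week-12 rating is therefore plausible. Its frequency is not given.

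**3. One course, two behaviours.** Suppose benefit fades on day 75. A patient who leaves is reinjected on day 80, was last rated on day 56 (improved), and the loss is never rated. A patient with the same course who waits is rated as lost on day 84.

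**4. What this does to the comparison if FEO has no effect.** Let p be the share who leave before the next rating. An arm's mean score is p × (leaver score) + (1 − p) × (waiter score), so

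spurious FEO − CO difference = (p_CO − p_FEO) × (waiter score − leaver score).

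The leaving rates are assumptions: 30% vs 10% (gap 0.20) and 50% vs 25% (gap 0.25). The document states no rule for scoring leavers, so four conventions are shown for the course in step 3.

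| Leaver scored at | Waiter scored at | Waiter − leaver (days) | Gap 0.20 | Gap 0.25 |
|---|---|---|---|---|
| last visit, 56 | midpoint, 70 | 14 | +2.8 | +3.5 |
| reinjection, 80 | first non-improved visit, 84 | 4 | +0.8 | +1.0 |
| last improved visit, 56 | last improved visit, 56 | 0 | 0 | 0 |
| reinjection, 80 | midpoint, 70 | −10 | −2.0 | −2.5 |

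The sign depends on the convention. These rows are illustrations, not limits. Pairing the last visit for leavers with the first non-improved visit for waiters, for instance, would give 28 × 0.20 = 5.6 and 28 × 0.25 = 7.0 days. If leavers are instead excluded as dropouts, the result is selective loss with no fixed direction.

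**The case against.** **Scoring belongs in the analysis plan.** The article says a full plan will follow, and how to score a patient reinjected before a rated loss is commonly settled there. This stands for the scoring rule. It does not stand for the rating itself, because Table 2 decides whether that rating exists.

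**Patient choice is not documented.** Section 2.9 says only that reinjection is received. Who decides, and on what criterion, is not stated. This stands: influence of the patient is an inference from the open-label design and the absence of a criterion.

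**Section 2.7 does not say that follow-up stops.** It applies a label, and Section 2.10 specifies intention-to-treat. This also stands. How these patients count is open.

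**Treatment-seeking is measured separately.** The BoNT interval is a secondary outcome, and controls use coconut oil with the same dosage and massage. Both are true and useful. Neither supplies a JRS rating at exit or removes patient expectation.

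**Stronger readings that the document does not support.** A reader might infer that knowing one is on coconut oil shortens the measured duration and favours FEO by about 19–23% of the planned effect (2.8/15 to 3.5/15). That rests on invented leaving rates and on scoring leavers at the last visit but waiters at the midpoint, a rule found nowhere in the article. A reader might also set the 62% against 35% for FEO (the mean of 0.623 and 0.080, the probabilities under 75 ± 15 and 105 ± 15) and see bias. That contrast assumes FEO works. With no effect, both arms are at 62%. Inflated false-positive rates, such as 11–41% at 32 per arm when 20–50% of controls and no FEO patients lose 14 days, likewise depend wholly on unsourced inputs.

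**Conclusion.** The point holds as a gap in data collection. Observation of a JRS-defined outcome can stop between visits without a blinded rating, in patients who know their arm. On the plan's control distribution, 62% of patients would lose benefit in the interval where this is most likely to happen.

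Whether it biases the comparison, and in which direction, cannot be settled from the article. Under the assumed leaving rates and the four conventions worked above, the spurious difference runs from about −2.5 to +3.5 days, including zero, against a planned 15 days. The result rests on three unknowns: who decides on reinjection, how often it precedes the next rating in each arm, and how such patients are scored. This is a cheap improvement worth making while recruitment runs (to February 2027), not a demonstrated bias in favour of FEO.

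**What to change.** 1. **Table 2.** Add a blinded JRS rating and the standard 5-minute video on the day of reinjection, before it is given, or at the first contact after another blepharospasm treatment starts.
2. **End of benefit.** Define it by JRS ratings only, with one rule for leavers and waiters in both arms. For example, treat the loss as lying between the last improved and the first non-improved rating.
3. **Patients still at least one point better at reinjection or other treatment.** Censor them at that date. Do not count them as having lost benefit or exclude them as dropouts, and reword Section 2.7 to match.
4. **Analysis.** The t-test and Mann–Whitney test need a single duration per patient, so use an interval-censored time-to-event comparison. This also accommodates the fact that the extra rating's timing depends on when the patient attends. Because leaving may be related to fading benefit, add a sensitivity analysis that counts reinjection as the end of benefit.

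The cost is a few minutes of evaluator time for patients who, if reinjected at the centre, are already attending, plus an amended Table 2 and a slightly longer analysis. When patients are treated does not change.
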